# STEM-PD trial protocol: a multi-centre, single-arm, first-in-human, dose-escalation trial, investigating the safety and tolerability of intraputamenal transplantation of human embryonic stem cell-derived dopaminergic cells for Parkinson’s disease

**DOI:** 10.1136/bmjopen-2025-107597

**Published:** 2025-12-30

**Keywords:** Clinical Trial, Parkinson-s disease, Neurosurgery

## Abstract

**ABSTRACT:**

**Introduction:**

Parkinson’s disease (PD) is a common neurodegenerative disease, which has extensive pathology that critically includes the loss of midbrain dopaminergic neurons. This loss leads to debilitating motor features such as bradykinesia and rigidity, as well as some non-motor symptoms. Intracerebral dopamine cell transplants have been explored for many years as a new approach to treating PD and initially used human fetal ventral mesencephalic tissue with inconsistent results, related in part to major logistical challenges in sourcing enough tissue of the right quality and the limited possibilities for quality control and standardisation. Dopaminergic neurons can now be derived reliably from human stem cell sources, which may overcome some of the challenges associated with fetal tissue transplantations.

**Methods and analysis:**

STEM-PD is a multi-centre, single-arm, dose-escalation, first-in-human advanced therapy investigational medicinal product (ATIMP) trial in Europe using a cell product that consists of dopaminergic neural progenitors derived from the RC17 human embryonic stem cell line. The aim of the study is to assess the safety, tolerability and feasibility of intraputamenal transplantation of this cell product in patients with moderately advanced PD. Eight participants will be recruited from two sites, Skånes University Hospital (Lund, Sweden) and Cambridge University Hospital (Cambridge, UK). The primary outcome of the trial is safety and tolerability, assessed by the number and nature of adverse events and serious adverse events, and the absence of space-occupying lesions on cranial MRI, in the first 12 months following transplantation. Secondary and exploratory outcomes, including clinical measures, changes in anti-Parkinson’s medication and measures of graft survival using positron emission tomography imaging, will be assessed at both 12 and 36 months post-grafting.

**Ethics and dissemination:**

Ethical approval was obtained from the Swedish Ethical Review Authority (EPM dnr 2021-06945-01) and South Central - Oxford A Research Ethics Committee (reference 23/SC/0243). Clinical Trial Authorisation was given by the Swedish Medical Products Agency (Dnr: 5.1-2022-57953) and the Medicines and Healthcare products Regulatory Agency for clinical trials authorisation (reference CTA 40773/0001/001-0001). Authorisation for transfer to Clinical Trial Regulation (EU) 536/2014 was given by the Swedish Medical Products Agency (Dnr: 5.1.1-2024-100773). Potential participants will receive verbal and written information about the trial and written informed consent will be obtained prior to enrolment. A lay summary of the results of the trial will be uploaded to the trial website which is publicly accessible. Trial results will be published in peer-reviewed journals.

**Trial registration numbers:**

NCT05635409.

STRENGTHS AND LIMITATIONS OF THIS STUDYFirst-in-human study to investigate the safety and tolerability of transplanting RC17 human embryonic stem cell-derived dopaminergic precursor cells into the brains of patients with Parkinson’s disease.A trial working across two centres in different countries to show feasibility across sites.The trial involves a single dose escalation after assessment of 6 months post-transplant safety data from a lower-dose cohort of four patients.Recruitment to trial from a previous long-running longitudinal observational trial (TransEuro), providing individualised disease trajectories for comparison pre- and post-grafting.The trial’s limitations are the small number of participants and the relatively short follow-up period in the first instance.

## Introduction

 Parkinson’s disease (PD) is a common neurodegenerative disorder that is characterised by the loss of midbrain dopamine (DA) neurons from the substantia nigra.^1^ These neurons modulate movement and certain aspects of cognition and therefore their loss leads to motor disabilities including bradykinesia and rigidity, as well as other motor and non-motor problems.^2^ There are currently no disease-modifying treatments for PD, and medical management is mainly focused on controlling the motor features using drugs that act on the dopaminergic system, such as levodopa (L-dopa) or DA agonists.^3^ Over time, these drugs become less effective and are associated with significant side-effects, including motor fluctuations, and for this, a number of other approaches have been used and are now in routine clinical practice (eg, deep brain stimulation (DBS) and dopaminergic infusion therapies).^4^ In addition, there is a significant non-nigral and non-dopaminergic pathology of PD which can significantly impact on quality of life.^5^ Thus, there is an urgent need for better treatments of Parkinson’s and a number of experimental approaches are being considered, including gene therapies, immune therapies, small molecules and drug repurposing approaches.^4^

One of the most promising potential PD therapies as an alternative to oral or enteral DA replacement medications has been DA cell replacement, using cells obtained from the developing human foetal midbrain.^6^ This approach has given inconsistent results, with some patients doing extremely well, exhibiting near-normal graft-derived dopaminergic innervation of the putamen and coming off all their anti-PD medication for years, while others have shown no or only modest clinical improvements.^7 8^ In some cases, patients also developed new involuntary movements called graft-induced dyskinesias (GIDs), which were so severe in a few patients that further neurosurgery with DBS was needed.^9^,^11^ These GIDs were thought to arise from the transplantation of serotonin neurons that develop adjacent to the DA cells in the human brainstem and that cannot be completely excluded in the dissection and tissue preparation.^12^ The inherent variation of cell quality using human fetal tissue also makes it impossible to properly quality control the product for grafting, as each patient will ultimately have a tissue implant derived from a unique collection of foetal material.^13^ Additionally, it is very challenging to source enough tissue for transplantation, as exemplified in the recent TransEuro trial of fetal tissue grafting for PD, in which 21 transplant surgeries were performed while 87 scheduled surgery slots were cancelled due to a lack of available tissue.^13^

To address these issues, a human stem cell-derived dopaminergic neural progenitor cell (the STEM-PD product) has been developed from the RC17 human embryonic stem cell line, which we will investigate as a DA replacement therapy through grafting into patients with moderately advanced PD in the STEM-PD clinical trial.^14^ This is the first such trial using this approach in Europe and the first to use this human embryonic stem cell line, but a similar approach has been undertaken by other groups who have recently published the results from their first-in-human trials.^15 16^

## Methods and analysis

### Overview

The STEM-PD trial is a multi-centre, single-arm, dose-escalation, first-in-human advanced therapy investigational medicinal product (ATIMP) trial. The aim of the study is to assess the safety, tolerability and feasibility of intraputamenal transplantation of the STEM-PD product in patients with moderately advanced PD.

Participants will be patients with moderately advanced PD who have been followed up for at least 12 months as part of the TransEuro observational study and who meet all inclusion and exclusion criteria as outlined in table 1^13^.

**Table 1 T1:** Inclusion and exclusion criteria for the trial

Inclusion criteria	Exclusion criteria
Have given written informed consent to participate in the trial	Tremor dominant disease, as assessed by the PI or other delegated clinician
Diagnosed with PD as defined using Queen Square Brain Bank criteria	Significant drug-induced dyskinesias as defined by a score of ≥2 in the Abnormal Involuntary Movement Scale (AIMS) dyskinesias rating scale, in any body part in the ON state
Moderate disease as defined by having Hoehn and Yahr stage 2–3 in OFF state	Ongoing major medical or psychiatric disorders, including depression (MADRS>20) and psychosis, or other medical unsuitability, as judged by the PI or other delegated clinician
Disease duration >10 years	Any contraindication to neurosurgery
Male or female, aged between 50 and 75 years (inclusive)	Unable to be imaged using MRI
Have a significant response to dopamine therapies as judged by the PI or other delegated clinician	Extensive ventral striatal loss or normal findings on F-DOPA PET at screening
Have symptoms that are not appropriately controlled by existing oral anti-PD medications, as judged by the PI or other delegated clinician	Significant cognitive impairment indicative of an incipient dementia/established dementia or values consistent with MoCA score of ≤24
Ability to travel to Lund for surgery	Unable to perform normal copying of interlocking pentagons and/or a semantic fluency score for naming animals of less than 20 over 90 s
Followed up for at least 12 months prior to inclusion in this trial in the TransEuro observational study	
Be fluent in English/Swedish to enable completion of questionnaires as assessed by the PI or other delegated clinician at Cambridge/Lund, respectively	
Be approved by the TMG clinical subgroup for trial participation	

F-DOPA, [18F]-fluorodopa; MADRS, Montgomery-Åsberg Depression Rating Scale; MoCA, Montreal Cognitive Assessment; PD, Parkinson’s disease; PET, positron emission tomography; PI, principal investigator; TMG, Trial Management Group.

Eight participants will be recruited, split into two equal cohorts (n=4), with the aim to graft 100 000 surviving DA neurons per putamen in the first cohort (3.54×10^6^ STEM-PD cells grafted per putamen) and 200 000 surviving DA neurons per putamen in the second cohort (7.08×10^6^ STEM-PD cells grafted per putamen).

The number of cells being grafted is based on studies suggesting these are the numbers of DA cells that need to differentiate and survive for a meaningful clinical benefit in PD.

The decision for the escalation of dose for cohort 2 will be undertaken once all four participants in the dose 1 group have reached the 6-month follow-up time point. The data relating to clinical evaluations, MRI scans and their 6 months [^18^F]-fluorodopa (F-DOPA) Positron emission tomography (PET) imaging will be reviewed by the Data and Safety Monitoring Board (DSMB) in conjunction with the clinical subgroup of the Trial Management Group (TMG). The DSMB will make a recommendation on how to proceed, and a decision will be made by the TMG around the progression to dose 2. The DSMB can also recommend waiting for additional data (eg, up to the 12-month follow-up with imaging) before making any recommendation.

Participants will be recruited from two sites—Lund, Sweden and Cambridge, UK, with all surgeries occurring in Lund using the same surgical device. Transplantation of the cells will be done bilaterally in a single session in a stereotactic neurosurgical procedure, using the Rehncrona-Legradi device for cell delivery into the putamen. This device is manufactured in-house at the Skåne University Hospital in Lund and is not CE marked, so it can only be used in this hospital (for more detail, see Barker *et al*^17^). This device has been shown to deliver developing DA cells accurately to the target site—the putamen^18^—and so we deemed it to be the best device to use in this trial given no approved and licensed device is available for cell delivery to the CNS. Given this, all UK participants will have to travel to Sweden and, to help support this, they will be accompanied by a caregiver and a medically qualified member of the UK trial team. Furthermore, their stage of disease has been chosen (after discussions with the ethical committees) such that they are fully ambulant when on medication, so they will be able to undertake this travel. This is part of the inclusion criteria.

The surgical procedure will use a stereotactic image-guided technique. Five targets for each putamen will be used, two in the anterior part and three in the posterior part of the putamen, divided as follows: one anterior to the anterior commissure; one at the anterior commissural line; and three posterior to the anterior commissure. The trajectories to those targets for each putamen will be made through one or more burr holes per side of the cranium, depending on the best trajectory to the target, and avoiding the ventricles and blood vessels, which will be imaged preoperatively using MRI. The trajectories will be placed to achieve maximal distribution of the graft tissue within the putamen. For dose 1, each tract will have four deposits, and for dose 2, each tract will have eight deposits. Each deposit will contain 2.5 µL of cell suspension (70 000 cells/µL).

The trial does not have any predetermined stopping criteria. However, premature termination would be triggered by concerns raised by the investigators and/or the DSMB regarding safety and ethical implications of continuing the trial. A temporary halt to further transplantations will be triggered if one participant develops a serious adverse event (SAE) judged to be possibly, probably or definitely related to the STEM-PD product, or if two participants develop any adverse reaction towards the cell product that is graded as severe. In the case of a temporary halt, all investigators, the DSMB and trial sites will be notified promptly. Regulatory authorities and ethics committees will be informed of the temporary halt within 15 days via a substantial amendment. If the trial is temporarily halted, the trial teams in Cambridge and Lund, and a representative of the Sponsor will need to make a formal decision to restart the trial, providing justification to do so. The DSMB will also be consulted prior to making this decision and will be asked to provide a recommendation on how to proceed.

### Patient and public involvement

An advisory panel comprised of five people with PD and carers reviewed and provided feedback on the research question, trial design and outcomes, and participant pathway for this research protocol. The advisory panel also reviewed the participant information sheets for clarity to ensure they were detailed enough and easy to understand, and a member of the panel attended the ethical committee meeting.

### Non-investigational medicinal products

The STEM-PD product is an allogenic cell product, and participants will therefore receive an immunosuppressant regimen for 12 months, with the standard agents used in solid organ transplantation regimes. The following agents will be used for all patients after surgery: tacrolimus (0.05 mg/kg two times per day), azathioprine (1 mg/kg once daily) and prednisolone (40 mg once daily for 12 weeks, following which it will be tapered to 10 mg daily). Additionally, participants will receive methylprednisolone (1 g intravenous) at the time of surgery and basiliximab (20 mg intravenous) on the day of surgery and on day 4 following transplantation. Prophylactic antibiotics will be administered around the time of surgery according to local guidelines, as well as trimethoprim-sulfamethoxazole three times per week for the duration of immunosuppression. Prophylaxis for osteoporosis with alendronic acid and calcium carbonate/vitamin D supplementation will also be administered for the duration of immunosuppression, as well as gastroprotection with a proton-pump inhibitor.

### Schedule of assessments

Participants will be followed up for 36 months following transplantation (figure 1). Preoperative assessments will include CT-angiography and MRI for surgical planning. Assessments of safety will be undertaken with a clinical examination and blood tests at each visit, with additional MRI brain imaging being undertaken at day 28, month 2, month 3, month 6, month 9, month 12, month 24 and month 36 following surgery.

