**General**																								
Informed consent	X																							
Assessment of eligibility	X																							
Concomitant medication (including PD medication)	X	X	X	X	X	X	X	X	X	X	X	X	X	X	X	X	X	X	X	X	X	X	X	
Height	X																							
Weight	X	X	X				X	X	X	X	X	X	X	X	X	X	X	X	X					
ECG		X				X																	X	
Vital signs		X		X	X	X	X	X	X	X	X	X	X	X	X	X	X	X	X	X	X	X	X	
Physical examination	X	X					X	X	X	X	X	X	X	X	X	X	X	X		X	X	X	X	
Demographics	X																							
Medical history	X																							
Years of education	X																							
Smoking status	X																							
AE assessment	X	X		X	X	X	X	X	X	X	X	X	X	X	X	X	X	X	X	X	X	X	X	
Pregnancy test†	X	X	X							X		X	X	X	X	X	X	X		X				
Provision of participant contact/alert card		X																						
Review nIMP compliance							X	X	X	X	X	X	X	X	X	X	X	X	X	X				
Enrolment to long-term F/U																							X	

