**Psychiatric assessments**																								
MADRS	X	X								X			X			X		X			X		X	
Non-motor/QOL assessments																								
PDQ-39		X																	X			X		X
EQ-5D-5L		X																	X			X		X
PD NMSS		X																	X			X		X
TREATMENT																								
Surgery (transplantation of STEM-PD product)				X																				
nIMPs			As prescribed (including tapering)																					

‘ON’ or ‘OFF’ dopaminergic medications are indicated for clinical assessments at each stage.

* The 15+ month visit will occur within 2 weeks of the participant completing their course of immunosuppressants. If the completion of immunosuppressants is within 2 weeks of the scheduled 18-month post-surgery visit, then this visit and the assessments listed will not take place.

† To be performed for female participants of childbearing potential only. At screening, a serum pregnancy test will be performed, and on all subsequent visits, either a serum or urine pregnancy test will be performed at the site’s discretion. Monthly urine pregnancy tests will be performed by participants at home at months 7, 8, 10, 11, 13, 14, 15, 16 and 17. A member of the trial team will contact the participant to confirm the pregnancy test has been performed and record the result.

‡ Samples will not need to be repeated on day −1 if performed within the 3 days prior to this visit, ie, to day −4). Blood typing does not need to be repeated.

§ To be performed depending on which immunosuppressant treatment the participant is on, that is, if the participant is on tacrolimus treatment, then the tacrolimus level will be tested, and if on ciclosporin A, the CyA level will be tested.

¶ At screening, will include a screening test of anti-HLA antibodies. If positive, a specific assessment of any major histocompatibility complex (MHC) class I antigens against those expressed in the STEM-PD product will be carried out. For all other visits, HLA antibodies will be monitored.

** Where possible, blood analysis will be performed on samples already collected.

†† For visits completed in Lund, this will be done simultaneously with the extended battery MRI

‡‡ Optional for Cambridge participants.

§§ Low dose CT scans will be performed in conjunction with each positron emission tomography scan performed at RS-SUS.

¶¶ To be videoed with the participant wearing a cap.

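### The text ends immunosuppression at 12 months but Table 2 at about month 15 to 18, and routine safety bloods stop at month 12

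*Protocol article*

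**What the plan says.** All references are to the protocol article.

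- **Duration in the text.** Under Non-investigational medicinal products: "participants will therefore receive an immunosuppressant regimen for 12 months". The agents are tacrolimus, azathioprine and prednisolone. The only taper described is prednisolone, reduced to 10 mg daily after 12 weeks.
- **Duration in Table 2.** The asterisk footnote reads: "The 15+ month visit will occur within 2 weeks of the participant completing their course of immunosuppressants". It goes on to a case in which that visit is dropped: "If the completion of immunosuppressants is within 2 weeks of the scheduled 18-month post-surgery visit". The treatment row for these drugs reads "As prescribed (including tapering)" and gives no end date. The row "Review nIMP compliance" is marked at 15+ and month 18. For women of childbearing potential, the dagger footnote adds: "Monthly urine pregnancy tests will be performed by participants at home at months 7, 8, 10, 11, 13, 14, 15, 16 and 17".
- **Safety assessments in the text.** Under Schedule of assessments: "Assessments of safety will be undertaken with a clinical examination and blood tests at each visit".
- **Safety assessments in Table 2.** Full blood count (FBC), urea and electrolytes (U&E), liver function tests (LFTs), CRP and tacrolimus/ciclosporin level are last marked at month 12. The 15+ column has no blood test and no physical examination. The footnote on drug levels says that "if the participant is on tacrolimus treatment, then the tacrolimus level will be tested".

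**The concern.** The article gives two different ends to immunosuppression, and the safety bloods follow the earlier one while the visit plan follows the later one. The 15+ visit exists because the course is ending. It includes vital signs, weight, concomitant medication, adverse-event assessment and compliance review, but no blood test or examination.

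The article lists clinically significant events that may be due to immunosuppressive treatment as adverse events of special interest (Assessments to be undertaken). If participants are still taking such drugs after month 12, the scheduled tests for effects on blood count, kidney and liver have already stopped. The end date also governs other treatment: the antibiotic prophylaxis and the bone protection are given for as long as immunosuppression lasts, so their end is unclear too.

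**Working it through.** **1. End of the course.** No formula applies; the statements are set side by side. The text says month 12. In Table 2, a visit labelled 15+ falls within 2 weeks of completion, and completion may fall close to month 18. Compliance review and site pregnancy testing both run to month 18 and then stop, and home pregnancy tests fill months 13 to 17. The schedule thus expects completion at about month 15 to 18. That range is inferred from the visit label and footnote; it is not a stated date.

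**2. Marks in Table 2.** The table has 23 visit columns: 4 up to and including surgery, 7 day columns and 12 month columns. Reading each row against them gives:

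| Row | Marks, day 1 to month 12 | 15+ | Month 18 | Months 24, 30, 36 |
|---|---|---|---|---|
| FBC, U&E, LFTs, CRP (each) | 14 | no | no | no |
| Tacrolimus/ciclosporin level | 14 | no | no | no |
| Glucose | 14 | no | yes | no |
| HbA1c | 4 | no | yes | no |
| Blood lipids | 9 | no | yes | no |
| HLA antibodies | 4 | no | yes | all three |
| Physical examination | 12 | no | yes | all three |
| Compliance review | 12 | yes | yes | no |
| Adverse-event assessment | 14 | yes | yes | all three |

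The 14 marks are 7 day visits (1, 2, 7, 14, 21, 28, 42) plus 7 month visits (2, 3, 4, 5, 6, 9, 12).

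**3. Could this be a shifted column?** No. Glucose lies in the same block, agrees with FBC at every visit through month 12, and is marked again at month 18 with 15+ blank. Physical examination shows the same blank at 15+.

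**4. Length of the gap.** Time on treatment after the last FBC, U&E, LFTs and CRP:

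- everything stops at month 12: 12 − 12 = 0 months;
- the course ends at month 15: 15 − 12 = about 3 months;
- the course ends at month 18: 18 − 12 = about 6 months.

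For comparison, the longest scheduled interval between these tests up to month 12 is 3 months (month 6 to 9, and 9 to 12). After month 12 there is no next test.

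**5. Who can still be affected.** Publication was on 30 December 2025, and 18 months earlier is about 30 June 2024.

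- Lower limit: the final graft was in October 2024, so month 15 falls in January 2026 and month 18 in April 2026. At least 1 participant had both ahead.
- Upper limit: assume the second cohort was grafted only after all four in the first had reached month 6. The latest first-cohort graft is then October 2024 − 6 months = April 2024, and month 18 came by October 2025. At most the 4 in the second cohort remain.
- Already past month 18: 8 − 4 = 4 to 8 − 1 = 7 participants.
- Draws at two per participant: 1 × 2 = 2 to 4 × 2 = 8. With 15+ placed at month 15, the 8 requires all four second-cohort grafts after about 30 September 2024. Only the final graft is dated that late, so 8 is a ceiling. Where 15+ is dropped, one draw remains for that participant.

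**The case against.** The strongest reply is that the worrying version depends on tacrolimus or azathioprine continuing past month 12, which the article nowhere says. A coherent alternative is that these stop at month 12 and only prednisolone is tapered afterwards. The drug-level row would then end where it should. This stands. A reader might infer from the plural in the asterisk footnote, or from pregnancy testing to month 18, that all agents continue. But the plural may simply name the whole course, and pregnancy tests do not show which agent is being taken. They also apply only to women of childbearing potential in a trial of people aged 50 to 75.

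Second, a journal article may leave agent-by-agent stop dates and taper steps to the full protocol. This also stands, and their absence is not criticised here. It does not excuse a printed duration that conflicts with the printed schedule.

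Third, the sentence promising examination and bloods at each visit is a loose summary, and the section then points to Table 2. It is inexact elsewhere too: no physical examination is marked at days 1 and 2, and baseline has no routine safety bloods. So it is imprecise wording rather than a rival instruction to sites. Correcting it is still worthwhile, because the visit at which it fails most plainly is the one tied to the end of immunosuppression.

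Finally, adverse events are assessed at all five visits after month 12, month 18 brings an examination with glucose, HbA1c and lipids, and most participants are already past these visits. All true. This limits the size of the point, but none of it supplies a blood count, kidney or liver test.

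**Conclusion.** The point holds as an inconsistency in the printed text with a limited safety-monitoring consequence. The 12-month duration conflicts with Table 2, and the promise of examination and bloods at each visit fails at 15+. Neither conclusion depends on which drugs continue.

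The size is 14 scheduled tests each for FBC, U&E, LFTs and CRP from day 1 to month 12, then 0 at five visits. That leaves about 3 to 6 months on some immunosuppressant without them if Table 2's timing is right, and no gap if the 12 months in the text is right. Missing drug-level tests are a fault only if a participant remains on tacrolimus or ciclosporin.

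It would go too far to conclude that participants are known to be on unmonitored tacrolimus or azathioprine, or that the trial's main result is compromised. The primary outcome covers the first 12 months, when monitoring is dense. Adverse events in months 12 to 36 are a secondary outcome, and their collection continues.

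The counts of participants assume that the escalation rule in the Overview was followed; only the first and final graft dates are given.

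**What to change.** 1. Under Non-investigational medicinal products, replace the 12 months with the actual end of the course, including the taper.
2. In Table 2, mark FBC, U&E, LFTs, CRP and a physical examination at 15+. Mark the drug level there only for a participant still on tacrolimus or ciclosporin.
3. Add the same bloods, on the same condition for drug level, to the existing month-18 draw for anyone still on or just finishing immunosuppressants. This also covers participants whose 15+ visit is dropped, without an extra visit.
4. Under Schedule of assessments, say that examinations and blood tests are done at the visits marked in Table 2.
5. For participants already past these visits, report when immunosuppression stopped and which safety bloods were taken after month 12.

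The cost is three text or table corrections, plus at most two routine draws and one examination for each of the one to four participants not yet past month 18 at publication. Month 18 already takes blood, so only the 15+ draw is a new venepuncture.
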